## Abstract

**Background:**

Adolescence can be a stressful and difficult period for young people and parents, with many changes occurring during this time, and a heightened risk of mental health problems for adolescents. The quality of parenting an adolescent receives and the relationship between parents and adolescents is of particular importance during this time and predicts adolescent outcomes. Parenting is a modifiable risk factor which can be targeted to improve outcomes for adolescents and their families. Many existing parenting interventions are group-based, which is not appropriate for all parents, leading to disengagement and dropout. Open Door created an intervention, the Open Door Approach to Parenting Teenagers (APT), an individual parenting programme for clinically stressed parents of adolescents. APT comprises six weekly 50-minute appointments, working with individuals or couples. To increase flexibility and maximise engagement, this intervention will be delivered both face-to-face and online. The preliminary evaluation of APT yielded promising findings for the feasibility, acceptability, and real-world effectiveness of APT. This randomised evaluation is a continuation of this.

**Methods:**

Participants will be parents of adolescents who self-refer to Open Door, reporting clinically significant levels of parenting stress through the SIPA. Participants will be randomly allocated to receive the APT intervention or waitlist control. The primary outcome measure will be the SIPA, measuring parenting stress, the parent-adolescent relationship, adolescent and parent wellbeing, and mental health outcomes. Secondary outcome measures measure mediators of change and adherence to APT. Results on outcome measures will be compared between the APT group and control group immediately following the intervention, three months post intervention, and six months post intervention.

**Discussion:**

If APT is an effective intervention compared with the waitlist control, this could improve outcomes for adolescents and parents, and be an accessible and engaging option for parents of adolescents.

**Trial registration:**

This trial is registered at the International Council on Harmonisation of Technical Requirements for Registration of Pharmaceuticals for Human Use Good Clinical Practice (ICH GCP), (Clinical Trial NCT03916172).

**Supplementary Information:**

The online version contains supplementary material available at 10.1186/s40359-026-04048-w.

## Introduction

### Background and rationale

Adolescence can be a challenging time for young people and their families, with many changes and difficulties often arising during this period. Adolescents have the highest rates of mental health difficulties of any age group, yet many adolescents do not access appropriate support [1]. During adolescence, conflict between adolescents and parents has been found to increase, affecting well-being and self-esteem [2, 3]. The challenges of parenting an adolescent can bring an increase in parental stress [4], which can impact parents’ health [5]. One effective way to improve outcomes for adolescents is to target and improve the quality of parenting an adolescent receives and improve the parent-adolescent relationship. Parenting interventions can reduce challenging and risk behaviours in adolescents, improve the parent-adolescent relationship, and reduce parenting stress [6, 7]. However, to date, the majority of parenting interventions are aimed at parents of younger children and are delivered in a group format. Group interventions can bring challenges, with parents reporting feeling judged and pressured to participate, and describing the stigma of attending a group parenting intervention a barrier to engagement [8, 9]. There is a need for an individual parenting intervention that can facilitate an improved therapeutic alliance, aiding treatment engagement [10]. Engagement difficulties have also been found in face-to-face interventions due to the time constraints attached to attending in person and the perceived stigma of being seen at a parenting intervention [11]. Digital interventions allow for increased privacy and time flexibility, as parents are not required to travel to and from sessions, with the potential to increase engagement [11, 12]. As parents’ preferences for face-to-face or digital interventions have been mixed, there is a need for a parenting intervention offering a flexible approach of both face-to-face and online sessions to meet preferences and engage more individuals [13].

This paper outlines the protocol for a randomised controlled trial (RCT) to measure the effectiveness of Open Door’s APT intervention. APT is a brief, manualised parenting intervention for clinically stressed parents of adolescents, with a particular focus on the adolescent-parent relationship. APT can be delivered face-to-face or digitally over six sessions. APT follows the Open Door APT manual, which is a six-session model. The APT manual contains guidance on applying APT to practice, core techniques, and step-by-step guides for sessions one to six as well as working with the adolescent and parent, working with couples, and additional considerations. Clinicians use the manual and follow a checklist for each session, which contains actions for each session.

Findings from its preliminary evaluation, a pre-post pilot study of 279 parents, demonstrated promising results, particularly in terms of feasibility, acceptability, and real-world effectiveness [14]. However, a significant limitation of this study was the lack of a control group and follow-up measures to demonstrate long-term effectiveness. Furthermore, as highlighted in intervention development frameworks [15, 16], an RCT is essential to establish the efficacy of an intervention and elucidate the mechanisms by which it achieves its effects. This trial will randomly assign parents to either an active group (complete the APT intervention immediately) or control group (placed on a waitlist). A waitlist control comparator group was chosen to ethically allow all participants access to the APT intervention while providing a baseline comparison against immediate treatment. Results on outcome measures will be compared between groups after the intervention, and at three and six month follow up intervals. This trial therefore builds on the pre-post study through ruling out spontaneous recovery and capturing long-term improvements. This trial will provide robust evidence regarding the effectiveness of a brief, individualised parenting intervention tailored for parents of adolescents. If effective, APT has the potential to offer a scalable solution to support parents and improve outcomes for adolescents and their families. By presenting this RCT protocol, this paper lays the groundwork for the next crucial step in establishing APT as a robust, evidence-based intervention.

### Objectives

The primary objective of this study is to evaluate whether APT is more effective than a waitlist control in reducing parental stress among clinically stressed parents of adolescents. Secondary objectives include assessing the impact of APT on parent-adolescent relationships, adolescent mental health, parental mental health, and parenting practices. Additionally, the study aims to evaluate the maintenance of these effects at three-month and six-month follow-up intervals. Mediators and moderators of treatment effects will also be explored to better understand the mechanisms of change. All participants will receive the APT intervention either immediately or after allocation to the waiting list, which may directly benefit the service user in reducing parental stress and improving the parent-adolescent relationship. Participants randomised into the APT intervention will benefit from receiving treatment earlier. We aim to assess engagement and acceptability, treatment fidelity and adherence to the APT model, and disseminate study outcomes to inform policymakers, commissioners and providers, to offer an effective evidence-based option for parents of adolescents.

## Methods: patient and public involvement, trial design

### Patient and public involvement

In planning this study we have been primarily guided by pressures the service faced from the local service user groups, the council and the CCG, to broaden the treatment options available for parents, with a need for individual face to face interventions. The APT intervention was developed through an ongoing consultation and collaboration with these bodies, who helped to identify the needs of the parents, allowing us to develop appropriate toolkits to include in the intervention. Through all stages of development of the intervention and the manual, ongoing feedback was sought from service users. This included the contents of the intervention, its length, and its usefulness, leading to the development of an intervention that reflected service users’ needs. For the preparation of the study design we consulted with both adolescent and parent service users to determine and assure relevance of the study, ways of involving both the parents and the adolescents in the research, and identify the most appropriate means of data collection. As a result of this consultation, the measures routinely used by Open Door were made available on both pen and paper and online/mobile, and an appropriate compensation model was developed. A steering group consisting of service users, members of the public, clinicians, academics and Open Door’s executives was created. Drawing upon the diversity of expertise, the members were instrumental in assisting us with the design of the study.

### Trial design

We propose a multi-site, 2-arm phase one superiority RCT, comparing APT to waitlist control, with an allocation ratio of 1:1.

## Methods: participants, interventions, and outcomes

### Trial setting

Recruitment for and delivery of the trial will be carried out in the United Kingdom at two clinical sites of Open Door Young People’s Consultation Service in a North London Borough.

### Eligibility criteria

Primary participants will be parents of adolescents who self-refer to Open Door. Adolescents will also be invited to take part in the study.

To ensure a focused and appropriate participant group, specific inclusion and exclusion criteria will be applied. Inclusion criteria requires that participants are parents of adolescents aged 11–18 years, with the adolescent residing with the parent for a minimum of two days per week. Additionally, parents must meet clinically significant levels of stress, as measured by the SIPA, and be proficient in English, to facilitate engagement with the intervention and assessment processes.

Exclusion criteria are designed to account for factors that could compromise the reliability of the study or interfere with the intervention’s applicability. These criteria exclude parents currently receiving treatment for psychotic illness or those who have previously received the APT intervention. Parents of adolescents with severe developmental disorders or life-threatening health conditions are excluded, as are those with adolescents currently receiving individual treatment at Open Door, to avoid potential overlap or confounding effects from simultaneous interventions.

The therapists providing APT have qualifications in psychology, psychotherapy or family therapy, and will undertake training and supervision in the APT model.

### Intervention and comparator

The aim of APT is to help the parent in the parenting of their adolescent and improve the adolescent-parent relationship. APT facilitates a collaborative relationship between the therapist and parent to develop parenting strategies, provide psychoeducation, and practice and reflect on behavioural experiments. Through this, APT aims to create a more balanced relationship between the parent and adolescent, where the adolescents’ views and feelings are considered, communication, boundaries and the relationship between parent and adolescent is explored, and the parent develops an enhanced understanding of their parental identity and role.

The APT intervention can be delivered one-to-one or with a couple. Participants will receive six weekly 50-min appointments, with the option of a 7th review session. Adolescents will be invited to attend one session; this is optional, and adolescents are not required to attend. The sessions will be delivered in person at one of the two clinical sites, or via video appointment. This allows for meeting parents’ delivery preferences to increase accessibility to the intervention.

Participants will be randomised into the APT intervention group or waiting list control group. Those randomised to waitlist will receive the APT treatment after no more than 25 weeks. Following randomisation, participants in the APT group will begin treatment. After six sessions of APT, the end-of-treatment battery will be administered to all participants (those in both APT and WL groups). The same battery will be administered to all participants again three months and six months following the end of treatment. After three months of randomisation, participants in the WL condition will be offered APT. These parents will be administered all test batteries from pre-treatment to six-month follow-up. Participants can withdraw from the study at any time. No concomitant care is permitted during the trial.

Fidelity of APT delivery to the APT model will be assessed through checklists completed by observers (see Outcomes section).
[figure not shown]

### Outcomes

The primary outcomes of interest in this study are changes in parental stress, the parent-adolescent relationship, and adolescent and parent wellbeing and mental health outcomes. These outcomes are measured by the primary measure, the SIPA, included in the parent battery. This is a 112-item self-report questionnaire structured into three main domain scores: Adolescent Domain; Parent Domain and Adolescent Parent Relationship Domain. A composite score (The Index of Total Parenting Stress) is computed from scores from all subsections. Scores are then classified into broad ranges: normal, borderline, clinically significant and clinically severe [17, 18].

Secondary outcome measures have been selected to explore mediators of change and adherence to the APT treatment model. The measures are grouped into four batteries: Parent, Adolescent, Psychotherapist, and Observer. Trial outcomes have been chosen due to their good psychometric properties and wide use in clinical practice and research [17–31].

### Parent battery

Strengths and Difficulties Questionnaire (SDQ): A brief behavioural questionnaire about the parent’s child. This contains 25 items, each scored from 0–2, measuring emotional symptoms, conduct problems, hyperactivity/inattention, peer relationship problems and prosocial behaviour. The total difficulties score is the sum of the first four subscales, with cut-offs as 0–13 within normal range, 14–16 borderline, 17–40 abnormal. The prosocial scale is scored separately, with higher scores indicating increased social behaviour [19].

Patient Health Questionnaire, 9-item depression module (PHQ-9): Each item is scored between 0–3, the total score is between 0–27, with 0–9 indicating mild low mood, 10–14 moderate low mood, 15–19 moderately severe low mood, 20–27 severe low mood [20, 21].

Generalised Anxiety Disorder Screener (GAD-7): Each of the 7 items is scored between 0–3, the total score is between 0–21, with 0–9 indicating mild anxiety, 10–14 moderate anxiety, 15–21 severe anxiety [22, 23].

Alabama Parenting Questionnaire-Short Form (APQ-SF): A 12-item, 5-point Likert self-report measure depicting parenting behaviours. This measures five dimensions of parenting: positive involvement with children, supervision and monitoring, use of positive discipline techniques, consistency in using positive discipline and use of corporal punishment. Higher scores on positive subscales indicate positive parenting behaviours, higher scores on negative subscales indicate poorer parenting behaviours [24–26].

Conflict Behaviour Questionnaire (CBQ): A 20-item questionnaire assessing perceptions of communication and conflict in the parent-adolescent relationship. Scores range between 0–20, with 1 point for responses indicating poor communication and conflict. Higher scores indicate higher levels of poor communication and conflict. We will be using the parent-report and adolescent self-report versions [27].

Parenting Scale: A 30-item questionnaire with a 7-point Likert scale measuring two parental discipline styles: Laxness and Over-reactivity, and measuring verbosity. Higher scores indicate poorer discipline practices [28, 29].

Reflective Function Questionnaire (RFQ): A brief screening measure of reflective functioning. This contains 8 self-report items with a 7-point Likert scale measuring certainty and uncertainty about mental states [30].

Working Alliance Inventory-Short Form-Client (WAI-SF-C): This measure will be used in the end-of-treatment battery. This is a 12 item, 7-point Likert scale, capturing three aspects of the therapeutic alliance: (a) agreement on therapy tasks, (b) agreement on therapy goals (c) development of an affective bond. Higher scores indicate a stronger therapeutic alliance [31, 32].

Goal Based Measure: Developed by CORC [33], used to rate patients’ accomplishment of their goals between zero to ten throughout treatment. Progress is tracked with zero indicating no progress, and ten indicating the goal has been achieved.

### Adolescent battery

Strengths and Difficulties Questionnaire Young Person Version (SDQ-YP): The self-report version of the SDQ. This also has 25 items, with each scored between 0–2, and measures emotional symptoms, conduct problems, hyperactivity/inattention, peer relationship problems and prosocial behaviour. Two versions that will be used: the 11–17 and the 18 +, depending on the age of the adolescent. The interpretation of the scoring is the same as the SDQ parent version.

Alabama Parenting Questionnaire Young Person Version (APQ-YP): This measures the adolescents’ perceptions of the parenting they receive. This also has 42 items, but ten are repeated to capture the adolescent's perception of both parents separately, with each item having a 5-point Likert scale. The interpretation of the scoring is the same as the APQ parent version.

Reflective Function Questionnaire (RFQ) [30] – See above.

### Psychotherapist battery

Working Alliance Inventory-Short-Form-Therapist (WAI-SF-T): a 12-item, seven point-Likert scale measuring the alliance elements described in the Parent Battery version. The interpretation of scoring is the same as the WAI-SF-C. This will be completed by APT therapists at the end of the treatment.

### Observer battery

To be administered by trial coordinators on a randomly selected intervention session's video:

Adherence to the APT model: Checklists to be filled in by observers for each of the six sessions, scoring one session per participant. Scoring will be performed by supervisors on a randomly selected intervention session video. The checklists capture actions for the therapist to undertake and components capturing the therapeutic stance, including level of activity of the therapist. Ten of these sessions will be rated by both coordinators to obtain appropriate levels of inter-rater reliability (> 0.9).

### Harms

During the consent process, it is explained to participants that any information that they disclose is confidential, with some exceptions, including if they disclose risk of imminent harm to themselves or someone else. For any service users presenting with high risk or safeguarding issues, Open Door’s standard procedure will be followed alongside the network to approach in case of emergencies, urgent referrals and safeguarding concerns. All research participants will be working with a trained mental health professional, who will receive weekly supervision with a highly specialised mental health professional. Should any unexpected risks or burdens arise, the participant will be able to discuss this with their therapist, who can discuss it with their supervisor and the research team (if necessary) to provide an appropriate solution.

### Participant timeline

(Fig. 1).

**Fig. 1 Fig1:**
[figure not shown]
Schedule of enrolment, interventions, and assessments*

#### Sample size

Sample sizes are calculated based on the primary outcome measure (SIPA) and our goal of ascertaining superiority of APT. The target sample size for this study is 80 participants, divided equally between the APT intervention and waitlist control group (40 participants per arm). This sample size provides 80% power to detect a medium-to-large effect size (d = 0.4) at a significance level of α = 0.05, while accounting for an anticipated attrition rate of 32.5%, as informed by the pilot study findings [14]. This sample size ensures that the study is adequately powered to evaluate the primary outcome of parental stress reduction. This sample size is achievable and able to capture the difference between arms.

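### The sample-size paragraph claims 80% power at d = 0.4, but 40 per arm with 32.5% attrition gives about 30% (unadjusted); 80% power is reached only at d of about 0.78

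*Protocol article*

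**What the plan says.** The claim is confined to one paragraph, Sample size. It bases the calculation on the SIPA and on showing superiority of APT. It then states: "The target sample size for this study is 80 participants, divided equally between the APT intervention and waitlist control group", that is "40 participants per arm". The power claim is "This sample size provides 80% power to detect a medium-to-large effect size", with the effect given as d = 0.4 and the significance level as 0.05, "while accounting for an anticipated attrition rate of 32.5%, as informed by the pilot study findings". It concludes: "This sample size ensures that the study is adequately powered to evaluate the primary outcome of parental stress reduction".

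Two other sections fix how d must be read. Trial design specifies a two-arm superiority trial with 1:1 allocation. Statistical methods makes the primary analysis a comparison of APT with waitlist on SIPA at post-intervention, through between-group mean differences. So d = 0.4 is a standardised difference between the arms. The paragraph gives no sidedness, baseline correlation or gain from repeated measures.

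**The concern.** N, effect size, α, power and attrition are all printed, so the claim can be checked directly, and a between-group d of 0.4 is far too small for 80 participants to detect with 80% power. The label is also a warning sign: by the usual convention d = 0.4 lies between small and medium, not between medium and large.

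The interpretation of the primary result is at stake. If APT has the effect the trial says it is powered for, an unadjusted analysis would miss it about seven times in ten. Readers told that the study is adequately powered would take a non-significant result as evidence that APT does not help. The Discussion says the findings will inform clinical practice and policy.

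**Working it through.** **Inputs.** From Sample size: 80 randomised, 40 per arm; d = 0.4 (so SD = 1); α = 0.05; attrition 32.5%; claimed power 80%. From Trial design: 1:1 allocation. Sidedness is not stated; two-sided is assumed and one-sided is also shown.

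**Step 1: completers.** 40 × (1 − 0.325) = 27 per arm, 54 in total.

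**Step 2: try to reproduce the 80%.** The noncentrality is d × √(n/2), and the normal-approximation power is Φ(d√(n/2) − 1.96).

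- n = 27: 0.4 × √13.5 = 1.470; Φ(1.470 − 1.960) = 31.2%.
- n = 40 (no attrition): 0.4 × √20 = 1.789; Φ(1.789 − 1.960) = 43.2%.

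The exact noncentral-t values, used from here on unless noted, are:

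| Completers per arm | Power at d = 0.4, two-sided | Power at d = 0.4, one-sided | Detectable d at 80%, two-sided | Detectable d at 80%, one-sided |
|---|---|---|---|---|
| 27 | 30.3% | 42.3% | 0.78 | 0.69 |
| 40 | 42.4% | 55.1% | 0.63 | 0.56 |

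The stated 80% is not reproduced. The most favourable reading that uses only stated inputs (one-sided, no attrition) gives 55%.

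**Step 3: the N that d = 0.4 needs.** n per arm = 2 × (1.960 + 0.842)² / 0.4² = 98.1, so 99; the noncentral t gives 99.1, so 100. In total 200 completers, and 200 / 0.675 = 296.3, so about 297 randomised (298 if the arms are to be equal).

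**Step 4: allow for baseline adjustment.** Adjusting for baseline SIPA with correlation r between baseline and outcome replaces d by d / √(1 − r²). The values of r are assumptions, since the article gives none. With 27 per arm, two-sided:

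| r | Power at d = 0.4 | Detectable d at 80% |
|---|---|---|
| 0 | 30% | 0.78 |
| 0.5 | 38% | 0.78 × √0.75 = 0.67 |
| 0.7 | 52% | 0.777 × √0.51 = 0.55 |
| 0.8 | 67% | 0.777 × √0.36 = 0.47 |

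The correlation that would give 80% is √(1 − (0.4/0.777)²) = 0.86. One-sided it is √(1 − (0.4/0.686)²) = 0.81. With no attrition, two-sided, it is √(1 − (0.4/0.634)²) = 0.78.

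**Step 5: where the 80 may have come from.** Two other calculations land close to it.

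- A two-group test at d = 0.8, which is Cohen's f = 0.4, needs 25.5 per arm, so 26, or 52 in total.
- A one-group pre-post test at a within-group d of 0.4 needs about 51 to 52.

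Then 52 / 0.675 = 77.04, so 77 to 78 randomised, near 80. At 54 completers each test has 82% power. Background and rationale describes the pilot as a pre-post study without a control group, which makes a within-group d plausible. The article does not show which slip, if either, occurred.

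**The case against.** The strongest reply is that 30% is the least favourable reading. The paragraph states no sidedness, and Statistical methods plans mixed-effects regressions that attend to baseline differences, so an unadjusted two-sided t-test may understate the power of the real analysis. This is fair as far as it goes: with r of 0.5 to 0.7 power is 38% to 52%, and the trial misses a true d of 0.4 about five to six times in ten rather than seven. It still does not approach 80% without a very strong correlation that the article does not claim. The later assessments do not supply the missing power: the primary comparison is at post-intervention, and Intervention and comparator says waitlist parents are offered APT three months after randomisation.

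A second objection is that the source of the error cannot be identified. This also stands. For example, a two-group, two-time repeated-measures test with f = 0.2 and r = 0.5 gives 80.7% at 52 participants, although that f corresponds to a 0.8 SD difference in change. The explanations in the working are therefore possibilities only, and the discrepancy does not depend on them.

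A third is that keeping N = 80 presumes the effect size is the wrong number. The sponsor could in principle hold to d = 0.4 and enlarge the trial, but that means about 297 randomised.

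Referring to a fuller protocol or analysis plan does not help. The issue is not an omission: the printed figures contradict one another under the printed design.

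**Conclusion.** The power statement is wrong as written. Under the stated design, 27 completers per arm give about 30% power at d = 0.4 (two-sided, unadjusted, equal attrition in both arms), against the claimed 80%. Unadjusted, the trial is sized for a large effect, d of about 0.78; with baseline adjustment at an assumed correlation of 0.5 to 0.7, for d of about 0.67 to 0.55. No reading that uses only the stated inputs exceeds 55%. The conclusion that the study is adequately powered for d = 0.4 should not stand, because it determines how a null result would be read.

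**What to change.** Keep N = 80 and rewrite the Sample size paragraph along these lines:

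> Forty parents per arm will be randomised, of whom 27 per arm are expected to provide post-intervention data. At two-sided α = 0.05 this gives 80% power for a between-group difference of d = 0.78 unadjusted, or about 0.55 to 0.67 with adjustment for baseline SIPA if the baseline correlation is 0.7 to 0.5. Power at d = 0.4 is about 30% unadjusted. A non-significant result will be interpreted from the confidence interval for the difference and not as absence of benefit.

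In addition:

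- State the test, its sidedness and any correlation the sponsor is prepared to assume and justify.
- If f = 0.4 was intended, write it as d = 0.8. If the 0.4 came from within-group change, say so and do not use it as a between-group effect.
- Remove the medium-to-large label for d = 0.4 and the claim of adequate power.
- Correct the registry entry if it carries the same statement.

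The cost is one reworded paragraph and a less favourable stated figure. No participants are added. The Recruitment section expects recruitment to finish in Summer 2026; the correction should be made before results are known.
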